### Sample size and power

Assuming a one-sided p-value of 0.025, power of 90% and a non-inferiority margin of 1.25, the total number of events is estimated to be 1266 for the three groups. Assuming a 1.5-year accrual and a maximum follow-up of 3.5 years with 99% ascertainment of vital status, and a 5.6% rate of mortality at 2 years, a total of 16,800 participants (5600 per treatment group) are required.

With this sample size, assuming a two-sided p-value of 5%, and a 35% treatment discontinuation rate with 60% exacerbation rate in the HandiHaler® group, the trial is able to detect an 8% reduction in the HR for first exacerbation with 90% power.

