**Figure 1 F1:**
[figure not shown]
**TIOSPIR® study design.** R, randomization; C, Close of study once the planned 1266 events have been reached; SMI, Soft Mist™ Inhaler. For patients who discontinue trial medication before the planned end of the trial, vital status follow-up continues every 12 weeks.

The eligibility screening visit may be the same day as the enrollment visit unless it is necessary to acquire off-site source documents. Participants are randomly assigned to one of the three treatment arms with equal probability using an interactive voice or web response system. Each patient is allocated a treatment box containing a unique medication number. The randomization schema is stratified by clinical center using a permuted block design with concealment of subsequent allocation.

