### Statistical design

The event-driven trial is designed to end when approximately 1266 deaths are reported. Based on expected mortality, the duration of the trial was estimated to be 3.5 years with 1.5 years enrollment period. The primary mortality analysis is to be conducted using all patients who were assigned treatment and took at least one dose of study drug, regardless of subsequent premature discontinuation of trial. Patients lost to follow-up are censored at the time of last known vital status. For the primary exacerbation analysis, patients are censored at the time of study medication discontinuation.

Mortality is the primary design variable that dictates sample size. The primary analysis includes both mortality and time to first COPD exacerbation, evaluated with the Cox proportional hazard model (with no covariate adjustment) using a hierarchical analysis scheme. This scheme requires that each null hypothesis be tested and rejected before proceeding to the next hypothesis to preserve the trial type I statistical error. The comparisons are to be tested in the following order compared with the HandiHaler® treatment group: 1) non-inferiority for time to death for Respimat® 5 μg; 2) non-inferiority for time to death for Respimat® 2.5 μg; 3) superiority for time to first COPD exacerbation for 5 μg Respimat®. The margin of non-inferiority is set at 1.25 (HR) based on practical considerations, i.e., if the upper bound of the 95% CI for the HR between Respimat® and HandiHaler® lies below 1.25, the null hypothesis is rejected.

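### The 90% power given for the 5 μg exacerbation test is per-test power; within the fixed testing sequence it is about 75% on stated assumptions

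*Protocol article*

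**What the plan says.** Statistical design in the Protocol article sets a hierarchical scheme: "This scheme requires that each null hypothesis be tested and rejected before proceeding to the next hypothesis". Three comparisons with HandiHaler follow in order: (1) mortality non-inferiority for Respimat 5 μg, (2) mortality non-inferiority for Respimat 2.5 μg, (3) superiority of Respimat 5 μg on time to first exacerbation. For the mortality tests the rule is that "if the upper bound of the 95% CI for the HR between Respimat® and HandiHaler® lies below 1.25, the null hypothesis is rejected".

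Two power statements then follow in the section Sample size and power. For mortality, the inputs are introduced by "Assuming a one-sided p-value of 0.025, power of 90% and a non-inferiority margin of 1.25", and "the total number of events is estimated to be 1266 for the three groups". For exacerbation, at that sample size, with a two-sided 5% level, 35% treatment discontinuation and a 60% exacerbation rate on HandiHaler, "the trial is able to detect an 8% reduction in the HR for first exacerbation with 90% power". That section does not mention the sequence, does not say that the figures are per test, and gives no power for reaching and rejecting the second or third hypothesis.

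**The concern.** Under the sequence, the exacerbation hypothesis can be rejected only if both mortality hypotheses have been rejected first. The trial's power for that claim is therefore the probability that all three tests succeed. For 2.5 μg mortality it is the probability that the first two succeed. If 90% is the power of each test taken alone, the design delivers less than 90% for the second and third claims.

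Time to first exacerbation is one of the trial's two primary endpoints, and 5 μg superiority on it is one of the two hypotheses in the Abstract. A reader who takes the statement at face value would put the chance of missing a true 8% hazard reduction at 1 in 10. Part of the extra risk comes from the mortality result of the other, investigational dose.

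**Working it through.** **Inputs from the Protocol article**
- Sample size and power: one-sided 0.025, 90% power, margin 1.25, 1266 deaths over three arms, 5.6% mortality at 2 years, 1.5 years of accrual, 3.5 years maximum follow-up, 99% ascertainment; for exacerbation, two-sided 5%, hazard ratio 0.92, 60% and 35% rates.
- Treatment arms (text after Figure 1): "Participants are randomly assigned to one of the three treatment arms with equal probability", so the two mortality tests share an equal-sized HandiHaler arm.

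**Step 1. Reproduce the mortality sizing.** Schoenfeld, true hazard ratio 1:

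4 × (1.960 + 1.2816)² / (ln 1.25)² = 844.1 deaths per pair of arms; × 1.5 = 1266.1 for three arms.

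This matches the stated 1266. The sizing is therefore for a single comparison, and it implies a true hazard ratio of 1, which the article does not state. The sample size also reproduces: with exponential mortality and uniform accrual the probability of death is 0.0761, and 1266 / 0.0761 / 0.99 is about 16,800.

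**Step 2. Reproduce the exacerbation figure.** Hazard ratio 0.92, two-sided 5%, 90% power:

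4 × (1.960 + 1.2816)² / (ln 0.92)² ≈ 6046 events in two arms.

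The article gives no time horizon for the 60% and 35% rates. Read as 2-year exponential rates with 2 to 3.5 years of follow-up, they give about 6224 events and 90.8% power. The stated 90% is thus recovered as the power of that test alone. Read as 3-year or 3.5-year rates, they give 85.3% or 82.3%. The steps below take the stated 90% as given.

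**Step 3. First mortality test.** 1266 / 3 = 422 deaths per arm. Standard error of ln HR = √(2/422) = 0.0688.

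Power = Φ(ln 1.25 / 0.0688 − 1.960) = 90.0%.

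**Step 4. Both mortality tests.** The shared arm contributes variance 1/422 to each contrast, whose total variance is 2/422, so the correlation is 0.5. The bivariate normal probability that both succeed is 0.8324, or 83.2%. A simulation of 2,000,000 draws gave 83.3%.

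**Step 5. All three tests**

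| Assumption | Chance of the 5 μg exacerbation claim |
|---|---|
| Mortality HRs 1, endpoints independent: 0.8324 × 0.90 | 74.9% |
| Mortality HRs 1, correlation 0.1 | 75.3% |
| Mortality HRs 1, correlation 0.5 | 77.3% |
| Mortality HRs 1, any dependence, lower bound: 0.8324 + 0.90 − 1 | 73.2% |
| Mortality HRs 1, any dependence, upper bound: the smaller of 0.8324 and 0.90 | 83.2% |
| Both mortality HRs 0.95, independent: 0.961 × 0.90 | 86.5% |
| Both mortality HRs 1.05, independent: 0.577 × 0.90 | 52.0% |

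The correlation is between the 5 μg mortality and 5 μg exacerbation statistics; that between 2.5 μg mortality and 5 μg exacerbation is taken as half of it.

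**Step 6. Share of the loss due to the second gate.** Behind the 5 μg mortality test alone, the exacerbation claim would have 0.90 × 0.90 = 81.0% under independence. The 2.5 μg gate takes the further 6 points or so, down to 74.9%.

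**The case against.** The strongest reply is that no printed number is wrong. The 1266 deaths, the sample size and the 90% for exacerbation all reproduce as single-test figures. Each power statement comes with its own test-level inputs, the gate is described openly in the section just before, and mortality is named as what drives the sample size. Quoting marginal power is common practice. An article also condenses a fuller protocol, and joint power could reasonably be left to that document.

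Much of this stands. A reader might infer an arithmetic error, but there is none. The absence of a joint power figure would not by itself be a fault in an article. What does not follow is that the sentence is right as it stands: it says without condition what the trial can detect, and a trial run under this sequence does not have that probability of making the claim.

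Three other stronger readings are tempting and are not supported:
- That 75% follows from the plan's inputs alone. It also needs independence of the two endpoints, which the article does not address, and mortality hazard ratios of 1, which are implied but not stated.
- That the 90% could simply be relabelled as power conditional on passing the mortality tests. Marginal and conditional power agree only under independence; at a correlation of 0.5 the conditional figure is 77.3 / 83.2, about 93%.
- That type I error is at risk, or that the trial must be enlarged. The fixed sequence protects type I error, and the point concerns only how power is stated.

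**Conclusion.** The point holds as a misstatement of what the 90% refers to. For a primary endpoint, the power within the sequence falls short of the printed figure by about 15 points under independence, so the chance of missing a true 8% hazard reduction is about 1 in 4.

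The shortfall itself does not depend on independence. At 1266 deaths and mortality hazard ratios of 1, the exacerbation claim cannot exceed 83.2%, however strong the exacerbation effect. Its size does depend on the true mortality hazard ratios: the range from 0.95 to 1.05 moves it far more than any plausible correlation. It also takes the stated 90% marginal power as correct; if the exacerbation and discontinuation rates refer to a horizon longer than 2 years, the figure under independence falls below 75%.

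**What to change.** In Sample size and power:
- Label both 90% figures as per-test marginal power.
- Add the power within the hierarchy: 90% for 5 μg mortality, about 83% for 2.5 μg mortality, about 75% for 5 μg exacerbation.
- State the assumptions: 1266 deaths, both true mortality hazard ratios 1, exacerbation hazard ratio 0.92 with 90% marginal power, and independent endpoints.
- Give the range: about 75% to 77% for correlations of 0.1 to 0.5, 73% to 83% under any dependence, and about 86% or 52% for mortality hazard ratios of 0.95 or 1.05 under independence.
- Do not call the 90% conditional power unless independence is stated with it.

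Sample size, test order and conduct do not change. The cost is a few sentences and a less favourable stated power.

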## Results

### Study progress

To train site investigators and staff, a total of 17 training meetings were conducted over a 6-month period at the initiation of the trial.

A total of 17,182 participants were randomized to treatment in more than 1200 investigator sites in 50 countries. Of these, 17,135 participants (99.7%) received at least one dose of medication, constituting the study population.

The trial was initiated in May 2010; enrollment was faster than expected and was completed in April 2011. Because of the quick enrollment, it is likely that the trial duration may be closer to 3 years than the originally expected 3.5 years. Final data collection for the primary outcome measure is anticipated in 2013.

## Discussion

The TIOSPIR® trial has several unique characteristics and presents challenges for the investigators. This is one of the largest COPD trials ever performed, and is being conducted on an international scope. The large size of the trial is dictated by two factors. First is the size of the study population required to assess mortality as an outcome measure, which is an uncommon event in ambulatory patients with COPD who are not oxygen-dependent [14]. Second, the primary outcome analysis is being conducted with a non-inferiority design comparing only active treatments. Thus, this trial is designed to provide a precise estimate of mortality rates as well as exacerbation rates. Another unique feature of this trial is that it compares the same active treatment tiotropium in different marketed delivery systems, formulations and doses to establish the impact of delivery system or dose on clinically rare outcomes, mortality and exacerbations.

This trial has many of the characteristics of a large-scale comparative effectiveness trial: all of the patients are taking active treatments; the inclusion criteria are broad and the study sites are widely representative of both academic and community practices; the outcome measures, mortality and exacerbation rates, are clinically relevant and have important economic implications; and participants are permitted to use their usual background treatments for COPD that do not replicate the class of drug used in the trial. Placebo is not included with the purpose of eliminating a differential drop-out bias, which can be induced by more exacerbations, worse symptoms, and possibly reduced life expectancy. The absence of a placebo group may also facilitate follow-up and drug adherence during a trial of relatively long duration. The duration of the trial (patients are be on treatment for between 2 and 3.5 years) allows for long-term data to be collected on safety and efficacy, including spirometry in the substudy. Thus, TIOSPIR® provides clinically useful information about the optimal use of tiotropium in COPD and guides clinicians, policy makers, and payers. Beyond that, the TIOSPIR® trial can provide information as to the validity of spirometry as a surrogate marker or predictor of efficacy in rare outcomes such as exacerbations.

Despite the organizational and logistic challenges of such a large trial, accrual of participants was faster than expected. This reflected the broad inclusion criteria that were designed to enroll patients who might be encountered in routine clinical practice. Patients with a medical history including MI, cardiac arrhythmia, or cardiac failure were generally included and only excluded if MI occurred within 6 months or less, if cardiac arrhythmia was unstable or life threatening, requiring intervention or a change in drug therapy during the past year, or if cardiac failure of New York Heart Association Class III or IV led to hospitalization during the past year. Moreover, all participants were assigned to an active treatment arm and were permitted to continue other background medications that did not interfere with study participation, and could participate in their usual care routine. One of the challenges in training the large number of investigators, many of whom were community practitioners, was to emphasize the statistical underpinnings of the trial, and the need for high levels of follow up whether or not patients remained on study drug. The study organization and oversight is similar to that used in other large multicenter trials and is designed to provide continuing monitoring and review of the data integrity and patient safety at several levels. This includes an SSC, a DMC, and a MAC that represent the international scope of the trial.

## Conclusions

In summary, the TIOSPIR® trial is designed as a large-scale international trial to ascertain the relative safety and efficacy of different formulations and doses of tiotropium in patients with COPD, based on mortality as the endpoint of highest relevance to clinical outcomes and patient safety, and to concomitantly determine the relative efficacy in preventing COPD exacerbations that are of high relevance to clinical outcomes and cost burden of COPD. This trial requires unique logistic, design, and statistical considerations that differ from smaller trials designed to measure bronchodilator efficacy. Moreover, this large cohort of COPD patients can provide important insights into the clinical epidemiology of COPD around the world.

## Appendix

Major Adverse Cardiovascular Events include the following:

· Stroke

· Transient Ischemic Attack

· Sudden Cardiac Death

· Myocardial Infarction

### Definitions of Major Adverse Cardiovascular Events

#### Stroke

Stroke is defined as an acute onset of focal neurological deficit of presumed vascular origin lasting for 24 hours or more or resulting in death. Additionally, an event lasting >24 hours is considered as a stroke if this is due to 1) therapeutic intervention by pharmacological or non-pharmacological means (i.e., thrombolytics, intracranial angioplasty), or 2) brain imaging available documents a new hemorrhage or infarct. The stroke is categorized as ischemic or hemorrhagic (based on imaging or autopsy) or type unknown. Fatal stroke is defined as death from any cause within 30 days of stroke.

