## Methods

### Study design

#### Outcome measures

The first primary endpoint for TIOSPIR® is all-cause mortality. Clinical sites follow all randomized patients for vital status until trial conclusion, including patients who prematurely discontinued study medication, and collect medical information regarding the date and cause of fatal events.

The second primary endpoint for TIOSPIR® is time to first COPD exacerbation. COPD exacerbations are defined as a complex of two or more respiratory symptoms (worsening dyspnea, cough, sputum production, chest tightness, or wheezing) related to the underlying COPD, with duration of 3 days or more, that require a change in treatment. Treatment changes include acute treatment with antibiotics and/or steroids, or an addition of new maintenance bronchodilator. Mild exacerbations are those that require new prescription of bronchodilator only, moderate exacerbations are those that require antibiotics and/or systemic corticosteroids without hospitalization, and severe exacerbations are those that lead to hospitalization. The onset date of exacerbations is defined by the onset of the first recorded symptom. Exacerbations that occur within 7 days of onset of a prior exacerbation are counted as a single exacerbation.

Secondary outcome measures will also be analyzed by treatment group to support inferences derived from the primary analysis. These measures include the number of COPD exacerbations, the time to first exacerbation associated with hospitalization, the number of exacerbations associated with hospitalization, and the time to the first major adverse cardiovascular event (e.g. fatal event in system organ classes cardiac and vascular disorders, myocardial infarction [MI], or stroke). Criteria for definition of major adverse cardiovascular events are specified in the protocol and are adjudicated by the site investigator who is masked to the study treatment (see Appendix). In a subset of approximately 1300 patients, spirometry was conducted at baseline and is repeated every 24 weeks. Patients in the substudy perform pulmonary function tests at a single time point in triplicate to record trough FEV_1_ and forced vital capacity (FVC). Tertiary analyses of treatment groups will be performed on subgroups specified by demographic variables, co-morbid conditions, disease severity, and concomitant medications.

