#### Transient Ischemic Attacks (TIA)

A TIA is defined as a rapid onset of a focal neurological deficit that resolves spontaneously without evidence of residual symptoms at 24 hours.

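### The added stroke clause in the Appendix covers only events over 24 hours, so it adds nothing for focal deficits and leaves some short events unclassified or labelled TIA

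*Protocol article*

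**What the plan says.** Time to first major adverse cardiovascular event (MACE) is a secondary outcome in the article's Outcome measures section. That section describes MACE by example ("e.g. fatal event in system organ classes cardiac and vascular disorders, myocardial infarction [MI], or stroke"), says the criteria are specified in the protocol and adjudicated by the masked site investigator, and refers to the Appendix.

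The Appendix lists four kinds of event: stroke, "Transient Ischemic Attack", sudden cardiac death and myocardial infarction. It then gives definitions:

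- **Stroke, first sentence:** an acute "focal neurological deficit of presumed vascular origin lasting for 24 hours or more or resulting in death". No treatment or imaging condition is attached.
- **Stroke, second sentence:** "Additionally, an event lasting >24 hours is considered as a stroke if this is due to 1) therapeutic intervention" (thrombolytics and intracranial angioplasty are the examples), or where "brain imaging available documents a new hemorrhage or infarct".
- **TIA:** a rapid-onset focal deficit that "resolves spontaneously without evidence of residual symptoms at 24 hours". Imaging is not mentioned.

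**The concern.** The second stroke sentence is presented as an extension of the first, yet it applies to events that the first sentence already captures. Its first condition is also hard to read literally, since it makes thrombolysis or angioplasty the reason why a deficit lasted beyond a day. Both features make sense if the sentence was meant for events shorter than 24 hours: a deficit cut short by treatment, or a brief deficit with a lesion on imaging.

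At stake is the classification of short, non-fatal neurological events. The trial was prompted by a safety question about one inhaler, so its cardiovascular outcome matters. Site investigators in more than 1200 sites judge these events. The only central adjudication that the article describes, the Mortality Adjudication Committee, reviews deaths. For non-fatal strokes, the article describes no later step that would correct a faulty definition. Some investigators could follow the literal text while others apply the presumed intent.

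**Working it through.** No sample size, power or error rate depends on this sentence, so the check is a case-by-case reading of the stroke and TIA definitions. The inputs are the first stroke sentence (24 hours or more, or fatal), the second (more than 24 hours, plus intervention or a new lesion), the TIA definition (spontaneous resolution, nothing residual at 24 hours) and the Appendix MACE list (which includes TIA).

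| Focal vascular event | Stroke, first sentence | Stroke, second sentence as printed | TIA | MACE under Appendix list |
|---|---|---|---|---|
| (a) 24 hours or more, any treatment or imaging | Yes | Adds nothing | No | Yes, as stroke |
| (b) Any duration, resulting in death | Yes | Adds nothing | Not needed | Yes, as stroke |
| (c) Under 24 hours, non-fatal, resolves spontaneously, new lesion on imaging | No | No (too short) | Yes | Yes, as TIA |
| (d) Under 24 hours, non-fatal, ended by thrombolysis or angioplasty | No | No (too short) | No (not spontaneous) | No |

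Three results follow.

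1. For focal vascular deficits the second sentence changes no classification. Rows (a) and (b) are settled by the first sentence, and rows (c) and (d) are outside the second sentence's time limit.
2. Row (d) is a true gap: it meets neither definition, so the event is lost from MACE.
3. Row (c) has a home, but under a different label. It is lost from the stroke component and kept in MACE through the TIA entry. The examples in Outcome measures do not name TIA.

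If the inequality in the second sentence is reversed, rows (c) and (d) both become strokes, rows (a) and (b) are unchanged, and the sentence does the work that its opening word announces. Row (c) would then meet both definitions, because the TIA definition does not exclude events that qualify as stroke.

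One qualification: the second sentence says only that an event must exceed 24 hours and does not repeat the requirement of a focal deficit. It could therefore add a long, non-focal event with a lesion on imaging. That does not help rows (c) and (d).

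**The case against.** The strongest reply is that this is a journal article. It says that the MACE criteria are specified in the protocol, which is not shown. An obviously illogical sentence may be a transcription slip that never reached the sites. This stands. The document does not establish which wording investigators used, so it cannot show that any event was misclassified. It does not remove the point: the article prints the definition in full and prints it wrongly, which is different from leaving detail to a longer document.

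Several stronger readings are tempting but not supported:

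- **Short events with a lesion on imaging are lost from MACE.** The Appendix lists TIA as MACE, and the examples in Outcome measures are open-ended. Those examples fail to name TIA; they do not exclude it.
- **Every short event with treatment or a lesion is misclassified.** A fatal event is a stroke whatever its duration.
- **As printed, the result varies with local access to imaging.** The printed rule makes imaging irrelevant for focal deficits. The corrected rule would make a short event's label depend on whether a scan was done. Dependence on access to thrombolysis is real under the printed rule.
- **A stated share of precision is lost.** Assuming that 5% to 15% of strokes are affected, the standard error of a log hazard ratio for stroke would grow by a factor of 1/√0.95 = 1.026 to 1/√0.85 = 1.085. The document gives no basis for that share and lists no separate stroke comparison. In time to first MACE, only row (d) events would be missing.
- **The treatment comparison is biased.** Treatment is double-blind and double-dummy, randomization is stratified by center and adjudicators are masked. The expected harm is lost events and inconsistency between sites, with no differential effect shown.

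**Conclusion.** The point holds as a definitional error of minor to moderate severity. As printed, the added stroke clause is redundant for focal vascular deficits. Non-fatal deficits ended within 24 hours by thrombolysis or angioplasty fall into no category and leave MACE. Short, spontaneously resolving events with a new lesion count as TIA instead of stroke.

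The effect is limited to time to first MACE and its stroke component, and the document gives no event rates from which to size it. All-cause mortality, time to first exacerbation, the target of 1266 deaths and the testing hierarchy are untouched. A reader might infer that a safety endpoint is seriously compromised; the document does not support that.

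The conclusion rests on a literal reading of the Appendix. The reversed inequality is inferred from the sentence's logic. Whether trial data are affected depends on the full protocol's wording.

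**What to change.** 1. Compare the sentence with the full protocol and with the text given to sites.
2. If only the article is wrong, publish a correction to the article.
3. If the protocol has the same error, reword the clause along these lines: *an event of less than 24 hours also counts as a stroke if (1) therapeutic intervention shortened it, or (2) available brain imaging shows a new infarct or hemorrhage*. Notify sites, and re-check reported TIAs and other short neurological events under the corrected rule, blinded to treatment and before unblinding.
4. Add to the TIA definition that the event must not meet the stroke definition, so that the two categories do not overlap.
5. Make the MACE description in Outcome measures agree with the Appendix list, stating explicitly whether TIA counts.

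The cost is a corrected sentence and two small consistency edits, plus a site notice and a blinded review of a limited set of events if the protocol is affected. The article describes a trial still collecting data, so the re-check can be done before unblinding; done afterwards, it would carry less weight.
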